## Abstract

**Background:**

Regular physical activity (PA) is a key contributor to healthy ageing. However, despite known health benefits, only one third of older adults in Germany reach the PA levels recommended for persons aged 65 years and above by the World Health Organization. The aim of the current study is to evaluate the effectiveness of two web-based interventions for the initiation and maintenance of regular PA (i.e., intervention groups 1 and 2) compared to a delayed intervention control group of older adults aged 65 to 75 years.

**Methods/Design:**

Study participants will be randomly assigned to one of three study arms in five communities in the Bremen-Oldenburg metropolitan region: a) Participants in the first arm will receive access to a web-based intervention for 10 weeks allowing them to track their weekly PA (subjective self-monitoring, intervention group 1); b) participants in the second arm will receive access to the web-based intervention for 10 weeks and, in addition, track PA using Fitbit Zips (objective self-monitoring, intervention group 2); c) participants in the delayed intervention control group will receive access to the intervention implemented in the first study arm after completion of the 12-week follow-up in the other two groups within each community. In addition, weekly group meetings in the communities will be offered to study participants in the intervention groups providing the opportunity to address questions related to the use of the website and to practice PA in groups (e.g., neighborhood walks, strength and balance exercises). To evaluate short-term effects of the intervention on physical and psychological health, PA, physical fitness, and cognitive and psychological variables will be assessed at baseline and 12-week follow-up.

**Discussion:**

This study will provide answers regarding acceptance and effectiveness of web-based interventions promoting uptake and maintenance of regular PA in persons aged 65–75 years. Study findings will contribute to a growing body of evidence in Germany concerning the role of community-based interventions for the promotion of PA and healthy ageing in older adults.

**Trial registration:**

German Clinical Trials Register DRKS00010052 (Date of registration 07–11-2016).

## Background

Regular physical activity (PA) is associated with improvements in physical, psychological, cognitive, and functional health [1–4]. The World Health Organization (WHO) and the American College of Sports Medicine (ACSM) recommend a weekly moderate exercise time of 150 min for adults aged 60 years and above. Moreover, it is recommended that older adults engage in flexibility and strength training at least two times per week [5, 6]. The percentages of older adults (aged 60 years and above) meeting the recommendation for moderate exercise time range from 2% to 83%, depending on the study [7]. In Germany, only 18% of adults between the ages of 60 and 69 years and 14% of adults between the ages of 70 and 79 years meet the current recommendations for PA [8].

Physical limitations due to health conditions or age-related restrictions, as well as a lack of age-appropriate PA programs and information regarding access to such programs, are barriers to program participation and to reaching PA recommendations in this population [9]. In contrast, high levels of personal motivation to stay physically and mentally active, as well as having access to affordable and appropriate exercise options, are perceived as facilitators for reaching and maintaining PA recommendations by older adults [9].

Interventions providing information on PA as print versions [10, 11] or face-to-face [12] have a long tradition and previous studies suggests that these interventions are effective in promoting PA in older adults. The increased use of the internet and mobile technologies in recent years may open up new opportunities for promoting PA in this population [13, 14]. In Germany, 50% of adults aged 60 years and above already use the internet regularly [15], 17% of adults aged 65 years and above use smartphones [16], and this trend is increasing. Hence, eHealth interventions (i.e., measures to promote health using information and communication technologies [17]), appear promising for reaching this population and for providing individualized PA programs. To date, a variety of studies (predominantly conducted outside of Germany) investigated the role of eHealth interventions to promote PA in older adults suggesting that participation in eHealth interventions leads to increased levels of PA [18–21].

Because a large body of evidence indicates that tailoring of intervention materials and messages to participants’ characteristics, such as gender, PA level at study entry, and readiness to engage in PA, is associated with greater success in achieving PA goals in the long-term [20, 22–26], intervention materials employed in the majority of the interventions in the above cited studies used tailoring. However, although a wide range of PA interventions is available in Germany [27], only few are tailored to characteristics and needs of older adults or readiness to engage in PA and the majority of studies investigating effects of PA interventions in this population demonstrated rather small behavioral changes [25]. Furthermore, the effects of self-monitoring of PA behavior via web-based diaries, logs or tracking devices have, thus far, not been systematically investigated in older populations in Germany.

Therefore, the main aim of the current study is to compare the effectiveness of two different web-based interventions (encouraging subjective vs. subjective and objective PA self-monitoring) among older adults living in five communities in the Bremen-Oldenburg metropolitan region to a delayed intervention control group. Recommendations regarding PA and intervention materials provided to participants of both web-based interventions will be tailored to gender, PA-level, and stage of readiness to engage in the interventions assessed at baseline. The study is embedded in the larger Physical Activity and Health Equity: Primary Prevention for Healthy Ageing (AEQUIPA) research network which is funded by the Federal Ministry of Education and Research (BMBF).

## Methods

### Aims of the overall AEQUIPA project and network

The network conducts theory-based and participatory empirical research in the Northwestern part of Germany (http://www.aequipa.de/en/home.html, [28]). It aims to develop, implement, and evaluate PA interventions for the primary prevention of chronic diseases in persons aged 65 years and above. With five subprojects, AEQUIPA’s goal is to strengthen the evidence base for preventive PA in the context of healthy ageing and to gain new insights into environmental, social-contextual, and individual factors influencing PA in persons aged 65 years and above. This study is one of five subprojects of the entire network.

### Study aims

The following main research question will be examined in this study:Is a web-based intervention with subjective and objective PA monitoring more effective for the promotion of PA among older adults than a web-based intervention with subjective PA monitoring only compared to a delayed intervention control group?

Secondary research questions of the study are the following:Do participants’ characteristics (e.g., age, gender, motivational stage) influence intervention attendance and PA behavior?Is participation in the web-based interventions associated with improvements in secondary outcomes, such as well-being, quality of life, fear of falling, physical and cognitive functioning?

An additional objective of the study is to improve our understanding of how web-based interventions and technologies for PA tracking ought to be designed to be usable for the target group and which features ought to be included from the user’s point of view.

### Selection of communities for the study

Preceding recruitment for this study and as part of another subproject of the AEQUIPA network (RTC project, see [29]), a cross-sectional community readiness assessment (CRA) regarding the uptake and/or implementation of PA interventions in older adults (65–75 years) was conducted in a sample of municipalities within the Bremen-Oldenburg metropolitan region. The CRA was based on a structured interview administered to key informants, such as representatives from local public authorities, senior citizen organizations or sports clubs in each of the selected communities [29]. Municipalities were selected for inclusion if they already had a comparably high proportion of older adults or if they expected a high increase in the proportion of older adults living in the region over the next decade. Overall, 23 municipalities (12 rural, 11 urban) were included in the assessment. The five communities with the lowest levels of community readiness were selected for the implementation of PA interventions (three urban communities: Burglesum, Bremen; Vahr, Bremen; Obervieland, Bremen; two rural communities: Osterholz-Scharmbeck, Lower Saxony; Achim, Lower Saxony).

### Participants and procedures

Names and addresses of men and women between the ages of 65 and 75 years residing in these five communities of the metropolitan region of Bremen-Oldenburg will be drawn from the records of the residents’ registration office. Subsequently, persons will be invited to participate in the study via mail. The study will also be publicized in local newspaper articles, in senior organizations, and as part of capacity building activities of the RTC project. Eligibility for study participation will be determined in telephone interviews with trained study nurses following the inclusion and exclusion criteria outlined below.

#### Inclusion and exclusion criteria

Residents of the five communities will be eligible for study participation if they are between the ages of 65 and 75 years, if they are able to live independently (i.e., in own apartment or room without assisted living, no regular home nursing), and if they provide an informed consent to participate in the study. Further criteria for inclusion in the study are basic knowledge of German, the ability to walk without a walking aid, and to participate in study assessments and weekly group meetings without external support. Also, internet access at home or at family members’ or friends’ houses is a precondition for participation. Participants will be excluded from the study if they have planned a vacation for more than one month during the intervention period, display cognitive impairment (Mini-Mental-Score ≤ 27) or other permanent impairments (e.g., stroke, neurological diseases, such as Parkinson’s) or if there are any medical contraindications regarding program participation.

After successful screening for study eligibility, study participants will be assigned to one of three study arms by the study nurses: a) a web-based intervention with subjective PA self-monitoring (intervention group 1), b) a web-based intervention with subjective and objective PA self-monitoring (intervention group 2) or c) a delayed intervention control group (waitlisted control group) receiving the intervention of intervention group 1 after completion of the 12-week follow-up (see Fig. 1 for the study design). Each intervention condition will be randomly assigned to certain weeks of baseline assessment. Participants will be free to choose from available time slots during a phone call with a study nurse, but only after their decision will they be informed about which intervention condition was assigned to this particular week.

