### Measures

Participants will be invited to the study center to complete baseline (T0) and follow-up assessments (T1). At the study center, participants will undergo different anthropometric, physical, motor and cognitive tests, as well as an assessment of motivational stages to engage in PA. Cardiovascular fitness will be assessed using the 2-min step test [30]. Functional status and physical performance will be measured employing the Short Physical Performance Battery (SPPB) which includes balance, gait speed, and chair raising tests [31]. Moreover, postural control under dynamic conditions [32], strength of the upper extremities [33], hand grip strength [34], height, weight, and body fat will be assessed using stadiometers and bioimpedance scales. Cognitive dysfunction [35], memory (Verbal Learning and Memory Test (VLMT), [36]), and attention and inhibition (Simon Task, [37]) will be assessed in cognitive tests. In addition, working memory updating and inhibition (Random Number Generation Test (RNGT), [38]), and postural control under static conditions (measure of tandem stand by use of iPad, software: Sensor Data, Wavefront Labs, [39]) will be assessed under single- and dual-task conditions. Motivational stages regarding PA will be measured via a validated algorithm [40, 41].

After both assessments, all participants will receive an accelerometer (ActiGraph GT3x+) to objectively measure PA and a self-administered questionnaire. Participants will be instructed to wear the accelerometer on the right hip and during the day for seven days following baseline and follow-up assessments. The self-administered questionnaire will contain validated instruments and self-generated items assessing levels of PA, perceived physical environment, social support, health behavior, quality of life, and previous experience with using technology (for further detail on the instruments included in the questionnaire, see Table 1). Sociodemographic information will include age, gender, migration background, education, employment, and household income. In addition, participants of intervention groups 1 and 2 will fill out a self-administered questionnaire at the follow-up comprised of self-generated items regarding use and acceptance of the website, attendance of the offered group sessions, and overall satisfaction with the interventions.

**Table 1 Tab1:** Measures in the self-administered study questionnaire

Outcome measure	Instrument/scale
Physical activity	

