One week after the baseline assessment, the intervention will be introduced to participants of intervention groups 1 and 2 separately in group sessions with a maximum of 24 participants. Five weeks after the start of the intervention, a second group meeting will be held to ensure the proper use of the website and the Fitbit Zips in the two intervention groups. After completion of the follow-up assessment, persons in the delayed intervention control group will receive access to the web-based intervention of intervention group 1. However, no weekly group meetings will be offered to participants in this study arm.

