### Analytic strategy

#### Quantitative analysis, sample size

Hierarchical linear regression models will be used to analyze the intervention effects. Due to the week-wise randomization scheme, recruitment week will be included as a clustering variable. Change over time in objectively measured PA will serve as the primary outcome variable. Change over time will be calculated by subtracting the baseline value from the follow-up value (PA_T1_-PA_T0_). To assess the intervention effects, two dummy variables for intervention groups 1 and 2 will be added contrasting the change over time in PA in each intervention arm with the changes in the delayed intervention control group. Expecting small to moderate intervention effects [45], we calculated the sample size assuming a standardized mean difference of 0.33 in change over time between the intervention groups and the delayed intervention control group. Further, assuming ten clusters (recruitment weeks) per study arm and an intraclass correlation of 0.01, 190 participants per study arm will be necessary for the analysis with α = 0.05 (two-sided test) and β = 0.20. Expecting a loss to follow-up of 20%, we aim for a sample size of *n* = 684 at baseline.

Changes in cardiovascular fitness, physical performance, body fat, cognitive dysfunction, fear of falling, and quality of life will be analyzed as secondary outcomes. Several variables will be included as potential confounders, such as baseline PA-level, age, gender, education, motivational stage, and other health behaviors. In additional analyses, the moderating influence of gender, socioeconomic strata, and motivational stage on intervention effects will be explored.

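### As written, participants know their arm before the baseline accelerometer week, so the T0 half of the T1 minus T0 contrast is avoidably open to arm-dependent behaviour

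*Protocol article*

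**What the plan says.** All references are to the protocol article.

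- **Randomisation** (Inclusion and exclusion criteria). The unit is the week: "Each intervention condition will be randomly assigned to certain weeks of baseline assessment".
- **Booking and disclosure** (same section). Participants pick their own slot by telephone with a nurse, and "only after their decision will they be informed about which intervention condition was assigned to this particular week". No other time of disclosure is given.
- **Nurses.** Under Participants and procedures, "Eligibility for study participation will be determined in telephone interviews with trained study nurses". Under Inclusion and exclusion criteria, once screening is passed, "study participants will be assigned to one of three study arms by the study nurses".
- **Baseline measurement** (Measures). Participants attend the study center for T0 tests. They then receive a questionnaire and an accelerometer, with the instruction to "wear the accelerometer on the right hip and during the day for seven days following baseline and follow-up assessments".
- **Start of intervention** (Interventions). "One week after the baseline assessment, the intervention will be introduced to participants of intervention groups 1 and 2 separately in group sessions".
- **Primary outcome** (Quantitative analysis, sample size). "Change over time in objectively measured PA will serve as the primary outcome variable", computed as the follow-up value minus the baseline value. Each intervention arm is contrasted with the delayed intervention control group.

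**The concern.** Telling participants the arm only after they have picked a slot stops them from choosing an arm. It does nothing for the measurements that follow. Someone who knows that a PA programme starts next week may begin early, or may hold back until it starts. Someone who knows they are wait-listed may carry on as usual, or start alone. Any such difference between arms in the T0 week enters the primary outcome with its sign reversed. The same knowledge can affect how diligently the device is worn.

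Some people may also not come to T0 once they know their arm. They would leave before any baseline data exist, so the 20% loss to follow-up, which is counted from the baseline sample of 684, does not cover them. The clustering term for recruitment week cannot correct attendance that depends on arm.

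Finally, the nurses who screen also book and assign. If they can see which condition a week carries, slot offers and eligibility judgements could follow it.

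**Working it through.** **1. Order of events.** Set side by side, the sections give this sequence:

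| Step | Event | Section |
|---|---|---|
| 1 | Telephone screening by nurses | Participants and procedures |
| 2 | Slot chosen by phone; condition told after the choice | Inclusion and exclusion criteria |
| 3 | T0 visit in the booked week | Inclusion and exclusion criteria; Measures |
| 4 | T0 questionnaire and seven days of accelerometer wear | Measures |
| 5 | Introduction session, one week after baseline | Interventions |

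Disclosure attached to step 2 precedes all of T0. If it were delayed to step 3, the T0 tests might be protected but the accelerometer week would not. Only disclosure after step 4 protects the baseline PA value, and nothing in the text places it there.

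**2. Effect on the estimate.** Let δ be the true difference in change (intervention minus control). Let b be the between-arm difference in T0 activity caused by knowing the arm, in SDs of the change score.

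- Unadjusted change score: observed effect = δ − b.
- Adjusted for baseline PA: observed effect = δ − s·b, where s is the slope of T1 on T0. With s between 0 and 1 the bias is smaller but not zero, because the covariate itself carries the shift.

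**3. Reproducing the planned sample size.** Inputs from Quantitative analysis, sample size: standardised difference 0.33, ten weeks per arm, ICC 0.01, two-sided α = 0.05, power 0.80.

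- df = 2 × (10 − 1) = 18; t quantiles 2.101 (0.975) and 0.862 (0.80).
- Without clustering: 2 × (2.101 + 0.862)² / 0.33² = 161.2 per arm.
- Design effect at 19 per week: 1 + (19 − 1) × 0.01 = 1.18.
- 161.2 × 1.18 = 190.3, which matches the stated 190.

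**4. Power and error rate under assumed shifts.** Standard error of the contrast = √(2 × 1.18 / 190) = 0.1114. Power is from the non-central t with 18 df. The article gives neither size nor direction for b, so the values are assumptions, and the table is for the unadjusted change score.

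| T0 rise b in an intervention arm | Observed effect if δ = 0.33 | Power |
|---|---|---|
| 0 | 0.33 | 0.80 |
| 0.05 | 0.28 | 0.66 |
| 0.10 | 0.23 | 0.50 |

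If intervention participants instead hold back at T0 by the same amounts and δ = 0, a false benefit of 0.05 or 0.10 appears. The two-sided rejection rate is then 0.07 or 0.14 instead of 0.05.

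**5. With baseline adjustment.** Assume s = 0.5 (not given in the article) and hold the SD fixed:

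- b = 0.05: 0.33 − 0.5 × 0.05 = 0.305, power about 0.74.
- b = 0.10: 0.33 − 0.5 × 0.10 = 0.28, power about 0.66.

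Adjustment would also reduce residual variance, so these powers are approximate. In either analysis a larger sample does not remove the bias.

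**The case against.** **Timing is inferred.** The article says the condition is told after the slot decision. A reader might infer that it is always told in that same call; the text does not say so, and the design figure is not available here. This stands against asserting same-call disclosure, and it weakens the points on non-attendance and on the T0 tests, which need disclosure before the visit. It does not rescue the accelerometer week, which follows the visit.

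**The trial is open anyway.** A reader might infer that T0 is the only part of the change score measured with knowledge of the arm. It is not: at T1 everyone knows whether they had the website, the tracker or the wait list. The accelerometer is also objective, so the risk is changed behaviour or wear, not biased scoring. Both points stand. T0 is singled out only because knowledge of the arm can be avoided there.

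**Nurses.** A reader might infer that allocation is not concealed from them. The roles described make it possible for them to know a week's arm, but the article does not say who holds the list or whether they see it while screening or offering slots. A condensed article may leave that to the full protocol.

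**Size.** The bias is one-for-one only without baseline adjustment. Baseline PA level is listed among the potential confounders, although the paragraph opens with the secondary outcomes, so its use for the primary analysis is arguable. The shifts are hypothetical, and early starting and holding back pull in opposite directions. All arms eventually receive a web-based intervention, which gives less reason to stay away. This stands: the bias is possible, not demonstrated.

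**Conclusion.** The point holds in a limited form. Followed as written, the procedure has baseline PA measured with knowledge of the arm, although the programme has not begun and nothing in the text explains why the arm must be known by then. This rests on the plain reading that disclosure follows slot choice, and for the accelerometer it survives disclosure as late as the T0 visit.

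The direction of any bias is unknown and its size cannot be taken from the article. On the assumed shifts of 0.05 to 0.10 SD, it is large enough to matter against a planned effect of 0.33: without adjustment power falls to between 66% and 50%, or the false-positive rate rises to between 7% and 14%. With adjustment the damage is smaller but does not vanish. The documents do not support saying that nurses know the arm when they screen or book, only that they could.

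**What to change.** - State when the arm is disclosed: after the T0 accelerometer week and the T0 questionnaire are complete, with the invitation to the introduction session.
- Hold that session after the last wear day of the group concerned.
- Keep the week-to-arm list from the screening and booking nurses until then, for example with the data manager.
- Analyse everyone who attends baseline in the arm of the booked week, and report by arm those who were booked but did not attend.

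Cost: a few sentences in the protocol and one extra contact per participant. Participants in all arms must keep the introduction date free, including wait-listed people who will not need it. Because sessions are held separately by arm with at most 24 people, and visit days differ within a week, a session may have to move by a few days.
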